**Figure 1 F1:**
[figure not shown]
The power analysis.

### Ethics approval

The study has received approval from the UNINOVE Human Research Ethics Committee (protocol number 15410 and 34248) and is registered with both the World Health Organization (Universal Trial Number U1111-1129-9338) and the Brazilian Registry of Clinical Trials (RBR-6XSB5H).

### Inclusion criteria

Patients undergoing surgical removal of impacted lower third molars will be included in the study if they agree to participate after reading and signing a statement of informed consent.

### Exclusion criteria

The exclusion criteria include: presence of systemic disease, chronic pain or neurological/psychiatric disorder; current smoking habit; use of anti-inflammatory agent, analgesic or bisphosphonate drug in the previous 15 days; pericoronitis in the previous month; pregnancy or current breastfeeding; or history of photosensitivity disorders.

### Randomization and composition of groups

After undergoing a clinical evaluation by the dental surgeons, patients who meet the eligibility criteria will be divided into five experimental groups (Figure 2) based on a randomization method involving raffle numbers. Randomization will be conducted by a researcher not involved in the recruitment and treatment of the participants. Concealed allocation will be performed using a set of random numbers placed in sealed opaque envelopes. The laser operator will open the envelope containing the procedure to be performed on each patient immediately following third molar surgery. Sealed envelopes awaiting new subjects will be kept in a safe place and given to the operator as the sessions are scheduled. The 40 patients will be allocated into four experimental groups or a control group as follows: Group 1 (660 nm laser, applied intraorally, n = 10), Group 2 (808 nm laser, applied intraorally, n = 10), Group 3 (660 nm laser, applied extraorally, n = 10), Group 4 (808 nm laser, applied extraorally, n = 10), Group 5 (control; no irradiation, n = 20).

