### Study design and composition of study sample

The study design will consist of five treatments evaluated on two occasions (at 2 and 7 days following surgery). Table 1 shows the scheme for repeated-measures analysis of variance. Because the measures of pain, swelling and mouth opening have low variability when using the proposed scales, 40 degrees of freedom will be sufficient to control for residual variance. Thus, a minimum sample size of 50 subjects (10 in each group) is sufficient. Thus 50 patients undergoing treatment at the center for the removal of impacted lower third molars will participate in the study.

**Table 1 T1:** Scheme for repeated-measures analysis of variance

**Causes of variation**	**Degrees of freedom**
Treatment	4
Period	1
Treatment × period	4
Residual	40
Total	49

In addition, as this work predicts a two-factor (two wavelength), two-group (two irradiation sites) analysis, there will be 20 patients in each group (10 in each experimental subgroup) and 20 in control group. The power analysis (Figure 1) shows that for medium and large effect size, the test power will remain above 0.8 for 20 subjects in each group.

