### Blinding procedures

The surgical procedures will be performed by two dental surgeons and a third person will perform both the preoperative evaluation and LLLT. Following a calibration exercise, three blinded examiners, who have not previously been involved in the evaluation, surgery or laser therapy, will perform the postoperative evaluations. The patients will be unaware of the group to which they are allocated.

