##### Surgical difficulty

The difficulty of the surgical procedure will be determined based on the Winter Classification, the Pell and Gregory classification and the modified Prant Classification. The Winter Classification [24] considers the alignment of the impacted tooth (vertical, horizontal, mesioangular, disto-angular, horizontal vestibular, or inverted). The Pell and Gregory scales [25] consider the position of the tooth on the occlusal plane (on a scale of A to C) and the ascending ramus of the mandible (on a scale of 1 to 3). The Prant scale modified by Amarillas-Escobar *et al.*[15] classifies the surgical procedure on a five point scale (grade I - extraction with forceps only, grade II - extraction by osteotomy, grade III - extraction by osteotomy and coronal section, and grade IV - complex extraction. At the end of the surgical procedures, the surgeons will classify the procedures and will record the duration of each operation from incision to final suture.

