### Statistical analysis

All data will be analyzed with respect to the normality of distribution using the Shapiro-Wilk test. Statistically significant differences between the experimental groups will be determined using analysis of variance, followed by a suitable post hoc test, if necessary. The significance level will be set at α = 0.05. By assuming normality in the distribution of the data, two-way ANOVA offers a high power for the design of this trial.

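### Surgical difficulty, operation time and surgeon are known before allocation is revealed, but the stated ANOVA uses none of them, which gives up precision in arms of 10 to 20

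*Protocol article*

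**What the plan says.** **Timing of allocation.** In the protocol article, Randomization and composition of groups: "The laser operator will open the envelope containing the procedure to be performed on each patient immediately following third molar surgery". Allocation uses raffle numbers in sealed opaque envelopes, and no strata are named. The four laser arms have 10 patients each (for example "Group 1 (660 nm laser, applied intraorally, n = 10") and the control arm has 20.

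**Difficulty and duration.** Under Surgical difficulty: "At the end of the surgical procedures, the surgeons will classify the procedures and will record the duration of each operation". The modified Prant scale starts at "grade I - extraction with forceps only" and ends at complex extraction. The eligibility sections set no limit by grade.

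**Surgeons.** Under Blinding procedures: "The surgical procedures will be performed by two dental surgeons".

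**Analysis.** Table 1 lists treatment, period, their interaction and residual. The Statistical analysis section adds: "Statistically significant differences between the experimental groups will be determined using analysis of variance", followed by a post hoc test, and it also refers to a two-way ANOVA. No covariate is named. Evaluation of results lists difficulty and duration among data to be recorded and gives them no role in the treatment comparison.

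**The concern.** The Background justifies the third-molar model by the damage that the operation does to bone, connective tissue and masticatory muscle. The extent of that damage is a plausible determinant of pain, swelling and mouth opening at 2 and 7 days, whatever laser is applied. A variable that predicts the outcome and is fixed before allocation can be put in the treatment model without risk of adjusting away a treatment effect.

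Two things are lost by leaving these variables out. The variance they explain stays in the error term and lowers power. And if the single randomisation that is run happens to be unbalanced on difficulty, the unadjusted contrast has no means of correcting for it. With 10 patients per laser arm, or 20 per wavelength or site margin, noticeable imbalance is not rare.

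**Working it through.** **1. Inputs.** From the document: arms of 10, 10, 10, 10 and 20; 20 per margin when wavelengths or sites are pooled (10 + 10); "The significance level will be set at α = 0.05"; two surgeons. Not in the document, and assumed: the share of hard operations, the outcome gap between hard and easy operations, and R2.

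**2. The plan's own power figure.** The sample size section says "for medium and large effect size, the test power will remain above 0.8 for 20 subjects in each group". Figure 1 is not shown, and the text gives no SD or correlation. Taking conventional sizes (medium f = 0.25, large f = 0.40), a one-way ANOVA of 3 × 20 gives power 0.37 and 0.78. A t-test of 20 versus 20 at d = 0.5 and 0.8 gives 0.34 and 0.69. A repeated-measures group-by-time test of 3 × 20 with an assumed correlation of 0.5 gives 0.93 and above 0.99. The stated figure can be neither confirmed nor refuted, and the point below does not depend on it.

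**3. Does omission inflate the type I error?** No. Simulating the 10/10/10/10/20 layout (20,000 trials per setting, correlation between covariate and outcome of 0.3, 0.5 and 0.7), the five-group F test rejects a true null in 5.0% of trials in each setting without the covariate, and in 5.0% to 5.2% with it.

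**4. Precision gained.** Adjustment multiplies the residual variance by 1 − R2, so the effective standardised difference is d/√(1 − R2). For d = 0.8 with 20 versus 20, the noncentrality is d/√((1 − R2) × (1/20 + 1/20)). Two-sided noncentral t, 38 df:

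| Assumed R2 | Effective d | Noncentrality | Power | Equivalent sample, 1/(1 − R2) |
|---|---|---|---|---|
| 0 | 0.80 | 2.53 | 0.69 | 1.00 |
| 0.1 | 0.84 | 2.67 | 0.74 | 1.11 |
| 0.2 | 0.89 | 2.83 | 0.79 | 1.25 |
| 0.3 | 0.96 | 3.02 | 0.84 | 1.43 |

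Taking 3 df off for covariates (35 df) changes each power by about 0.002. For the weaker five-group F test with a 0.5 SD shift in all laser arms, simulated power goes from about 0.24–0.25 unadjusted to 0.27, 0.32 and 0.46 at assumed correlations of 0.3, 0.5 and 0.7.

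**5. Chance imbalance.** The SD of a chance difference in a standardised covariate is √(1/n1 + 1/n2): 0.45 (10 v 10), 0.39 (10 v 20) and 0.32 (20 v 20). The chance of a difference of at least 0.5 SD is 26%, 20% and 11%. If half the operations are hard (assumed), two groups of 20 differ by 20 points or more in that share with probability 0.27, by exact binomial calculation.

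**6. What a given imbalance does.** If hard operations differ by g within-class SDs (assumed 1 to 1.5), a 20-point imbalance moves the contrast by 0.2g/√(1 + 0.25g²) = 0.18 to 0.24 SD. One standard error of a 20 v 20 contrast is √(2/20) = 0.32 SD, so the shift is within ordinary sampling error. Among 10 v 20 comparisons with a covariate imbalance of 0.5 SD or more, the unadjusted error rate is 7%, 11% and 16% at correlations of 0.3, 0.5 and 0.7. Over all randomisations it averages 5%.

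**The case against.** **This may be left to a full plan.** A journal article condenses, and covariates are often set in the SAP. That would be decisive if the article were silent on the model. But Table 1 lists the sources of variation line by line (4 + 1 + 4 + 40 = 49) and the sample size section relies on the 40 residual degrees of freedom. The point is that a better model than the printed one is available from data already collected. A fuller plan may already contain it.

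**A reader might infer that surgical trauma will pass for a laser effect.** The document does not support that. Allocation is random and concealed, the average error rate holds, and imbalance can hide an effect as readily as mimic one.

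**A reader might infer a case mix running from forceps-only to complex.** The article lists the categories of a scale, not a distribution. Entry requires surgical removal of impacted teeth, and the Background says that this damages bone, so a large forceps-only share is doubtful. A narrower mix would lower R2. This objection stands and limits what can be said about size.

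**A reader might infer that the grade is contaminated by knowledge of allocation.** Nothing shows this. The surgeons grade, a different person opens the envelope, and the lower grades are defined by what was done. The document only leaves the order of the two steps unstated.

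**Conclusion.** The stated analysis omits three prognostic factors that are fixed before allocation is revealed, two of which the plan already records. The validity of the test is not at stake: its average type I error is about 5% with or without them. What is lost is precision, along with protection against chance imbalance in the realised trial.

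The size is uncertain because R2 is unknown. At assumed R2 of 0.1 to 0.3, power for d = 0.8 with 20 versus 20 rises by 5 to 15 percentage points, equivalent to 11% to 43% more patients. If difficulty explains little, the gain is small, and so is the cost. This is a cheap improvement worth making, not a defect that undermines the trial.

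**What to change.** 1. State that the modified Prant grade and the operation time are written down before the laser operator opens the envelope. This puts their baseline status beyond question.
2. Prespecify, before analysis, a small covariate set in the treatment model for pain, swelling and mouth opening: difficulty grade and/or operation time, plus surgeon. Grade and time probably overlap, so one of them may be enough. Choose without reference to outcome data by group.

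The cost is protocol and analysis-plan wording, plus making sure that the operating surgeon is noted for each patient. About 2 to 3 residual degrees of freedom are spent: from the 40 in Table 1, 37 to 38 remain. The article reports that data collection is under way, so step 1 can apply only to patients still to be treated, while step 2 can apply to all.

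Dividing the remaining envelopes by grade is not advised. The grade is known only after surgery, so the operator would have to choose between envelope sets at that moment. That adds a step to the concealment process and could disturb the fixed 10/10/10/10/20 allocation. Covariate adjustment gives most of the benefit without that risk.

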**Methods/Design:**

After meeting the eligibility criteria, 60 patients treated at a Specialty Dental Center for the removal of impacted lower third molars will be randomly divided into five groups according to the type of laser therapy used at the end of surgery (intraoral irradiation with 660 nm laser; extraoral irradiation with 660 nm laser; intraoral irradiation with 808 nm laser; extraoral irradiation with 808 nm laser and no irradiation). To ensure that patients are blinded to the type of treatment they are receiving, the hand piece of the laser apparatus will be applied both intraorally and extraorally to all participants, but the device will be turned on only at the appropriate time, as determined by the randomization process. At 2 and 7 days after surgery, the patients will be evaluated by three blinded evaluators who will measure of swelling, mouth opening (muscle spasm evaluation) and pain (using two different pain scales). The 14-item Oral Health Impact Profile (OHIP-14) will be used to assess QOL. All data will be analyzed with respect to the normality of distribution using the Shapiro-Wilk test. Statistically significant differences between the experimental groups will be determined using analysis of variance, followed by a suitable *post hoc* test, when necessary. The significance level will be set at α = 0.05.

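### The planned total is given as 60, 50 and 40, so the enrolment target and the allocation ratio contradict each other, although most of the text points to 60 with 20 controls

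*Protocol article*

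**What the plan says.** The abstract (Methods/Design) states that "60 patients treated at a Specialty Dental Center for the removal of impacted lower third molars will be randomly divided into five groups".

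The first paragraph of Study design and composition of study sample sets out five treatments: "The study design will consist of five treatments evaluated on two occasions (at 2 and 7 days following surgery"). It concludes that "a minimum sample size of 50 subjects (10 in each group) is sufficient", and continues: "Thus 50 patients undergoing treatment at the center for the removal of impacted lower third molars will participate in the study". Table 1 in that section has 40 residual and 49 total degrees of freedom, and the text rests the sample size on those 40.

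The paragraph after Table 1 describes a different layout: "there will be 20 patients in each group (10 in each experimental subgroup) and 20 in control group". The power statement, above 0.8 for medium and large effects, is made for 20 subjects per group.

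Randomization and composition of groups says "The 40 patients will be allocated into four experimental groups or a control group as follows". The list that follows begins with "Group 1 (660 nm laser, applied intraorally, n = 10"), gives Groups 2 to 4 the same size, and ends with "Group 5 (control; no irradiation, n = 20").

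**The concern.** Total sample size and allocation ratio are basic design facts, and here neither is stated in only one way. Allocation uses sealed envelopes prepared in advance, so total and ratio determine what the set must contain. Fifty at 1:1:1:1:1 holds 10 control allocations; sixty at 1:1:1:1:2 holds 20. The article gives no other rule for when enrolment is complete, so the stated total is the only published benchmark. With both 50 and 60 in the text, a final count at either number could be described as planned.

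The size of the control arm also matters for the analysis, because every laser-versus-control comparison depends on it.

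**Working it through.** **Inputs**
- Abstract: total 60, five groups.
- Study design and composition of study sample, first paragraph: five treatments, 10 in each group, 50 taking part.
- Same section, paragraph after Table 1: 20 per group (10 per experimental subgroup) and 20 controls.
- Randomization and composition of groups: total 40; arms 10, 10, 10, 10 and 20.
- Table 1: 4, 1, 4 and 40 degrees of freedom, total 49.

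**Step 1. Sum the arms and compare with the totals**

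| Place | Stated total | Sum of stated arms | Control arm | Ratio |
|---|---|---|---|---|
| Abstract | 60 | not given | not given | not given |
| Study design, first paragraph | 50 | 5 × 10 = 50 | 50 − 4 × 10 = 10 (implied) | 1:1:1:1:1 |
| Study design, paragraph after Table 1 | not given | 2 × 20 + 20 = 60 | 20 | 1:1:1:1:2 |
| Randomization section | 40 | 4 × 10 + 20 = 60 | 20 | 1:1:1:1:2 |

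The 50 agrees with its own group size. The 40 does not agree with its own list: it is 60 − 40 = 20 short, exactly the size of the control arm.

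**Step 2. Which design Table 1 belongs to**

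4 + 1 + 4 + 40 = 49 = 50 − 1. Table 1 therefore goes with the 50-patient total, not with 60.

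**Step 3. What would change if 50 were run**

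The laser arms have 10 patients each under both versions; only the control arm differs. The standard error of a difference in means, in units of the outcome SD, is √(1/n₁ + 1/n₂). This assumes a common SD, one time point, complete follow-up and no covariate adjustment.

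| Comparison | Control 20 | Control 10 | Ratio |
|---|---|---|---|
| Four laser arms pooled (40) v control | √(1/40 + 1/20) = 0.274 | √(1/40 + 1/10) = 0.354 | 1.29 |
| One laser arm (10) v control | √(1/10 + 1/20) = 0.387 | √(1/10 + 1/10) = 0.447 | 1.15 |

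**Step 4. Reach of the power statement**

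It is made for 20 per group. A control arm of 10 is outside it. The text gives no numerical effect size, SD or correlation between visits, so the power figure itself cannot be reproduced from the text, and nothing here depends on it.

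**The case against.** The best defence is that the intended design can be largely recovered. The abstract, the paragraph after Table 1 and the only arm-by-arm list all give or sum to 60, and the last two give 20 controls. On this view 50 is only a minimum, which can coexist with 60, and 40 is a slip for the irradiated patients alone.

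Part of this stands. The weight of the text does favour 60 at 10/10/10/10/20. But the minimum reading of 50 fails at the next sentence, which says that 50 will take part. The irradiated-only reading of 40 is a plausible origin, but the sentence names the control group among its destinations. Condensing a protocol into an article explains omissions, not incompatible totals.

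A reader might infer more than the documents support:
- **That a control arm of 10 is stated.** No sentence says so; it follows from five groups of 10 totalling 50.
- **That envelopes were prepared for 50, or that precision has been lost.** The article does not give the size of the envelope set, and the arm list in the randomisation section sums to 60. The standard-error figures are conditional on the 50-patient version being run.
- **That recruitment is continuing, or that its end could be shown to be data-driven.** Trial status says only that data collection is under way, and the article describes no interim analysis or stopping rule.
- **That the number cannot be determined at all.** Figure 2, captioned as showing the sample composition, was not available and may give the arm sizes, although it could not remove the conflict in the text.

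**Conclusion.** The plan is wrong as written. Three totals (60, 50, 40) and two allocation ratios stand in current text, and the randomisation sentence contradicts its own list by 20 patients. Most of the text points to 60 at 1:1:1:1:2, so the conflict can be resolved, but the article does not resolve it.

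The consequence is conditional. If the 50-patient version were run, the standard error against control would rise by about 29% for the pooled laser arms and 15% for a single laser arm, under the assumptions in the working, and the power statement would not apply to the control arm. If 60 at 10/10/10/10/20 is operative, there is no loss of precision, and what remains is a misstated target and a sample-size justification built on the wrong total.

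**What to change.** First confirm, against the approved protocol and a count of the envelope set, which number is operative. Then state that number and its ratio everywhere.

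- **If it is 60 at 10/10/10/10/20:** replace the 40 in Randomization and composition of groups, and the 50 and the 10-in-each-group wording in the sample-size section. Rewrite Table 1 and the argument from 40 residual degrees of freedom, which otherwise stay on the 50-patient design. For 60 patients measured at two times there are 120 observations and 119 total degrees of freedom: treatment 4, patients within treatment 60 − 5 = 55, period 1, treatment by period 4, within-patient residual 55 (4 + 55 + 1 + 4 + 55 = 119).
- **If only 50 allocations were prepared:** say so, and restate the abstract, the control arm size, the ratio and the power statement to match.

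Either way the cost is a text correction, a revised table and an envelope count. No patients are added if 60 is already operative. If 50 is operative, moving to 60 would mean ten more controls, which is a design change and should be reported as one.

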**Figure 2 F2:**
[figure not shown]
Flowchart characterizing the experimental design, sample composition, and trial protocol.

### Blinding procedures

The surgical procedures will be performed by two dental surgeons and a third person will perform both the preoperative evaluation and LLLT. Following a calibration exercise, three blinded examiners, who have not previously been involved in the evaluation, surgery or laser therapy, will perform the postoperative evaluations. The patients will be unaware of the group to which they are allocated.

### Experimental protocol

#### Preoperative evaluations

##### Personal data

Information on gender (male/female), ethnicity (Caucasian, mixed race or African descent), education (illiterate to completed postgraduate) and age (years) will be collected prior to surgery by the laser operator.

##### Surgical difficulty

The difficulty of the surgical procedure will be determined based on the Winter Classification, the Pell and Gregory classification and the modified Prant Classification. The Winter Classification [24] considers the alignment of the impacted tooth (vertical, horizontal, mesioangular, disto-angular, horizontal vestibular, or inverted). The Pell and Gregory scales [25] consider the position of the tooth on the occlusal plane (on a scale of A to C) and the ascending ramus of the mandible (on a scale of 1 to 3). The Prant scale modified by Amarillas-Escobar *et al.*[15] classifies the surgical procedure on a five point scale (grade I - extraction with forceps only, grade II - extraction by osteotomy, grade III - extraction by osteotomy and coronal section, and grade IV - complex extraction. At the end of the surgical procedures, the surgeons will classify the procedures and will record the duration of each operation from incision to final suture.

